## Abstract

**Background:** The treatment of knee osteoarthritis, which is a major cause of disability among the elderly, is typically selected from multidisciplinary options, including complementary and alternative medicine. Moxibustion has been used in the treatment of knee osteoarthritis in Korea to reduce pain and improve physical activity. However, there is no sufficient evidence of its effectiveness, and it cannot therefore be widely recommended for treating knee osteoarthritis. We designed a randomised controlled clinical trial to evaluate the effectiveness, safety, cost-effectiveness, and qualitative characteristics of moxibustion treatment of knee osteoarthritis compared to usual care.

**Methods/designs:** This is a protocol for a multicentre, pragmatic, randomised, assessor-blinded, controlled, parallel-group study. A total of 212 participants will be assigned to the moxibustion group (n = 106) and the usual care group (n = 106) at 4 clinical research centres. The participants assigned to the moxibustion group will receive moxibustion treatment of the affected knee(s) at 6 standard acupuncture points (ST36, ST35, ST34, SP9, Ex-LE04, and SP10) 3 times per week for 4 weeks (a total of 12 sessions). Participants in the usual care group will not receive moxibustion treatment during the study period. Follow-up will be performed on the 5th and 13th weeks after random allocation. Both groups will be allowed to use any type of treatment, including surgery, conventional medication, physical treatment, acupuncture, herbal medicine, over-the-counter drugs, and other active treatments. Educational material that explains knee osteoarthritis, the current management options, and self-exercise will be provided to each group. The global scale of the Korean Western Ontario and McMaster Osteoarthritis Index (K-WOMAC) will be the primary outcome measurement used in this study. Other subscales (pain, stiffness, and function) of the K-WOMAC, the Short-Form 36v2 Health Survey, the Beck Depression Inventory, the Physical Function test, Patient Global Assessment, and the Pain Numerical Rating Scale will be used as outcome variables to evaluate the effectiveness of moxibustion. Safety will be assessed at every visit. In addition, an economic evaluation and a qualitative study will be conducted as a mixed-methods approach.

**Discussion:** This trial may contribute to developing evidence for the effectiveness and safety of moxibustion for treating knee osteoarthritis.

## Background

Osteoarthritis (OA) is the most common form of arthritis in the elderly, and it is characterised by pain and functional limitation, leading to a reduction in quality of life [1,2]. It is an active disease process involving the focal loss of articular cartilage, subchondral bone thickening, and new bone formation [3].

Non-steroidal anti-inflammatory drugs (NSAIDs) and acetaminophen are the most common pharmacological agents used to treat OA. However, according to recent studies, these products only help to slightly reduce short-term pain and do not inhibit disease progression [4,5]. Furthermore, these drugs are associated with adverse events, such as gastrointestinal irritation and bleeding, perforating ulcers, and renal and hepatic toxicity. Therefore, patients who experience unsatisfactory results and a risk of adverse events using pharmacological agents are recommended to pursue non-pharmacological treatments, including complementary and alternative medicines, such as acupuncture and moxibustion [6].

Moxibustion is a traditional oriental therapy that treats diseases through thermal stimulation by burning herbs, primarily *Artemisia vulgaris*, at specific spots on the skin [7]. It has been used for various diseases, such as OA, stroke, and hot flushes, in addition to acupuncture in the traditional medical systems of Korea, China, Japan, Vietnam, and Mongolia [8].

Acupuncture has been studied sufficiently to demonstrate that it has benefits for peripheral knee osteoarthritis (KOA) [6,9]. One systematic review evaluated acupuncture for peripheral joint OA and included 14 randomised controlled trials (RCTs) for KOA (a total of 18 RCTs); acupuncture was shown to be efficacious for pain control in KOA in sham-controlled RCTs [6]. In the Cochrane review, the authors concluded that acupuncture for peripheral joint OA had statistically significant and clinically relevant benefits in waiting list-controlled trials [9].

However, according to a recent systematic review [10] on the use of moxibustion for rheumatic conditions, only 4 RCTs [11-14] on KOA using moxibustion have been published, and it is difficult to provide conclusive evidence for the effectiveness of moxibustion in treating rheumatic conditions, including KOA because of a high risk of bias with low methodological quality. Therefore, high-quality studies following the CONSORT 2010 Statement and revised STRICTA are necessary to determine whether moxibustion is an effective treatment for KOA [15,16]. In addition, even if a placebo moxibustion procedure was developed, a successfully validated placebo moxibustion method that could be used in a double-blind RCT does not yet exist [17,18]. Thus, a pragmatic design using a usual care group is appropriate for evaluating overall effectiveness in a moxibustion trial [19].

More than half of Doctors of Korean Medicine (DKMs) use moxibustion to treat KOA [20], and moxibustion is one of the most common complementary and alternative medicines in Korea [21]. Because of the wide prevalence of moxibustion in Korea, it is necessary to evaluate the economic worth of moxibustion for treating KOA, and a qualitative study is needed in addition to the quantitative approach to understand why KOA patients seek moxibustion treatment and how they regard moxibustion treatment performed by a DKM.

Our study will therefore take a pragmatic approach and use a process of randomisation to assess the effectiveness and safety of moxibustion for treating KOA compared to usual care with a sample size calculated on the basis of a previous pilot study. Moreover, an economic analysis will be evaluated to assess the economic value of moxibustion in Korea, and a qualitative study will be conducted to understand the patient's experience and perspective on the use of moxibustion to treat KOA.

## Methods/design

### Objective

The aims of this study are as follows: (1) to assess the effectiveness of moxibustion treatment for treating KOA on the occurrence of pain, function, depression, quality of life, and adverse events compared to usual care and (2) to assess the cost-effectiveness and cost-utility of moxibustion in addition to usual care in the treatment of KOA patients and explore how KOA patients experience moxibustion in Korea.

### Design and setting

This is a multicentre, pragmatic, randomised, assessor-blinded, controlled, parallel-group study. From May 2011 to November 2011, 4 clinical research centres in Korea will participate in this trial: the Korea Institute of Oriental Medicine (Daejeon University Hospital) in Daejeon, Gachon University Gil Oriental Medical Hospital in Incheon, Dongshin University Gwangju Oriental Hospital in Gwangju, and Semyung University Oriental Medicine Hospital in Jecheon. The population of each city is greater than 140,000, and the estimated prevalence rates of KOA are 14.9% over 40 years old [22] and 38.1% over 65 years old [23] in Korea. Recruitment will therefore be expected to be completed within the study period. To recruit the participants, we will advertise in the media (daily papers, local newspapers, and public newsletters), in each hospital, and on the internet homepages of hospitals and public institutions. Eligible participants will be randomly allocated into 2 groups (the moxibustion group or the usual care group) with a 1:1 allocation ratio and receive treatment for 4 weeks with 2 months of follow-up (Figure 1). The evaluation of participants and the analysis of the results will be

[figure not shown]

performed by professionals blinded to the group allocation. Written consent will be obtained from each participant before the start of this trial. We will obtain oral and written consent from each participant before collecting information at the first visit.

## Types of participants

### Inclusion criteria

A total of 212 participants with KOA will be recruited from the outpatients of the acupuncture and moxibustion clinics of the 4 hospitals. We will include participants who have average daily pain over 40 points (on a 0- to 100-point scale) and have been diagnosed with idiopathic KOA according to the clinical guidelines of the American College of Rheumatology. The guidelines include patients currently experiencing pain in one or both knees with at least 3 of the following 6 conditions: 1) aged 50 to 70 years, 2) morning stiffness within 30 minutes of waking, 3) crepitus, 4) bony tenderness, 5) bony enlargement, and 6) no palpable warmth.

### Exclusion criteria

Participants will be excluded if they are experiencing or have a history of the following: inflammatory diseases,

including rheumatoid arthritis; cancer; traumatic injury that might be related to the current knee pain; autoimmune disease; uncontrolled hypertension; diabetes mellitus requiring insulin injection; life-threatening cardiovascular or neurological events within the past year; chronic respiratory disease; a haemorrhagic disorder; alcohol or drug addiction; an active infectious disease, including tuberculosis; keloidosis; a significant knee joint deformity; knee replacement surgery for the affected knee; knee arthroscopy within the past 2 years; steroid injection in the knee joints within the past 3 months; viscosupplement injections in the knee joints within the past 6 months; joint fluid injection within the past 6 months; and acupuncture, moxibustion, cupping, or herbal medicine within the past 4 weeks.

### Randomisation and allocation concealment

Randomisation will be performed using a computerised random number generator through the stratified block randomisation method of the SAS package (Version 9.1.3; SAS institute Inc., Cary, NC, USA) for sequence generation prepared by a statistician ([name]) with no clinical involvement in this trial. According to the Kellgren/Lawrence Scale of anterior-posterior (AP) and lateral standing knee radiographs, a random number will be stratified using a random block size of 4. Sequentially numbered, opaque, sealed assignment envelopes will be delivered to each research centre. Random allocation will be performed at the second visit for participants who provide informed consent and meet the criteria for inclusion. If a participant can be included in the study, the researcher will open the corresponding envelope in front of the participant. The corresponding envelopes will be opened only after the enrolled participants have completed all baseline assessments. Although participants and practitioners will be aware of the allocation arm according to the routine care setting, the outcome assessors and the data analysts will be kept blinded to the allocation.

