#### **Discussion**

Moxibustion and acupuncture have been widely used to treat the pain and functional limitations of KOA in Korea [20]. Some trials [11-14,34] have been conducted to evaluate the effectiveness of moxibustion in treating KOA in Korea and China. Moxibustion and NSAIDs were compared in 3 RCTs [11-13], combination therapy (moxibustion plus NSAIDs) and NSAIDs were compared in 1 RCT [14], and moxibustion and a hot pack were compared in 1 RCT [34]. According to these trials, single or combination moxibustion therapies increased the total response rate and decreased symptoms of pain in KOA patients. However, the processes of random sequence generation and allocation concealment were not reported in 4 trials [11,13,14,34]. Moreover, none of the trials used valid and reliable assessment tools, such as the WOMAC, and assessor blinding was not described. It is therefore not possible to exclude the possibility of a high risk of bias and determine the effectiveness of moxibustion treatment for KOA.

Concealment is the most critical factor of the allocation process, and a high risk of bias is generated by unconcealed allocation [35,36]. In a recent well-designed systematic review of acupuncture for chronic pain, only RCTs that used an unambiguous method of allocation concealment were included [37]. Therefore, we designed our protocol with adequate methodology of random sequence generation and allocation concealment using validated assessment tools, such as the WOMAC, SF-36, and BDI, and monitors will regularly evaluate whether the trial is being conducted according to the planned protocol.

Mixed-method research is the most recent systematic approach of using 2 or more research methods to answer a single research question. This approach has the advantages of expanding the understanding of the procedure's effects and verifying results from another perspective compared to an approach using a single method because the supplemental component enhances the validity of the study [36,38]. This method has been used to determine the effectiveness of interventions in recent studies on complementary and alternative medicine [39-41]. To comprehensively understand the effectiveness of moxibustion for KOA patients, we will conduct not only a quantitative

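### The protocol names one block size (4) for site-opened, unblinded 1:1 allocation, so a person who tallies a list could be certain of up to one third of upcoming assignments

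*Protocol*

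**What the plan says.** All but one of the relevant statements are in the Protocol, Randomisation and allocation concealment.

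- **Block size and stratum:** the stratification factor is the Kellgren/Lawrence grade read from knee films, and the rule given is "a random number will be stratified using a random block size of 4". No second size is given, the number of grade strata is not stated, and centre is not named as a stratification factor.
- **Envelopes:** "Sequentially numbered, opaque, sealed assignment envelopes will be delivered to each research centre". At allocation, "the researcher will open the corresponding envelope in front of the participant".
- **Timing:** "The corresponding envelopes will be opened only after the enrolled participants have completed all baseline assessments".
- **Blinding:** "participants and practitioners will be aware of the allocation arm". Outcome assessors and data analysts are to be blinded.
- **Ratio** (Design and setting): "with a 1:1 allocation ratio".

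The Discussion sets the standard that the trial claims to meet: "Concealment is the most critical factor of the allocation process, and a high risk of bias is generated by unconcealed allocation".

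**The concern.** Opaque envelopes hide an assignment only if it cannot be worked out from those already opened. With 1:1 blocks of one known size, the end of each block is determined by its beginning. The beginning is visible here: the envelope is opened openly at the centre, and one arm attends 12 treatment sessions while the other attends none.

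There is also room to act on a deduction. Table 1 places the knee radiograph, the eligibility check and the treatment expectancy questionnaire at visit 1. Under the section text, staff may therefore know a patient's stratum and attitude to moxibustion before the envelope is opened. Some exclusions call for judgement, such as significant joint deformity or uncontrolled hypertension. A person who could foresee the next arm could enrol, defer or exclude accordingly.

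Blinding the assessors does not help, because it acts after enrolment. The planned ANCOVA adjusts for the baseline measurement and centre. It would not remove a difference in expectancy that those two variables do not capture.

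**Working it through.** **Inputs.** From the protocol: block size 4; ratio 1:1, so two of each arm per block; 212 participants, with 32 at one centre and 180/3 = 60 at each of the other three (Sample size). Assumed, because the protocol is silent: separate lists per centre, and one to five equally frequent Kellgren/Lawrence strata. The protocol gives no predictability figure to reproduce.

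**Step 1: complete blocks of 4.** There are 4!/(2!2!) = 6 equally likely sequences and 6 × 4 = 24 places. A place is certain when one arm's quota of two is already used up.

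| Place | Sequences in which it is certain | Best-guess success |
|---|---|---|
| 1 | 0 of 6 | 1/2 |
| 2 | 0 of 6 | 2/3 |
| 3 | 2 of 6 (first two the same) | (1/3)(1) + (2/3)(1/2) = 2/3 |
| 4 | 6 of 6 | 1 |
| All | 8 of 24 = 33.3% | 2.833/4 = 70.8% |

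Without any knowledge of the sequence, best-guess success would be 50%. One third of 212 is about 71 participants.

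**Step 2: incomplete blocks.** A list that ends partway through a block loses some of its determined places. Simulation with centres of 32, 60, 60 and 60 and patients falling at random into the assumed strata gives:

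| Strata per centre | 1 | 2 | 3 | 4 | 5 |
|---|---|---|---|---|---|
| Certain | 33.3% | 31.7% | 31.0% | 30.2% | 29.4% |

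The lower end is 0.294 × 212, or about 62 participants. If one block were spread over several centres, staff at one site would see only part of it and the share would be lower.

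**Step 3: alternatives.** Fixed sizes were enumerated exactly. Mixed sizes were simulated for lists of 32 and 60 without a grade split. The observer was taken to know the set of sizes but not their order.

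| Scheme | Certain | Best-guess success |
|---|---|---|
| Fixed 4 | 33.3% | 70.8% |
| Fixed 6 | 25.0% | 68.3% |
| Fixed 8 | 20.0% | 66.6% |
| Mixed 4 and 6 | 5.5% to 5.8% | about 69% |
| Mixed 4, 6 and 8 | about 2.0% | about 68% |

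Mixing removes most of the certainty but little of the guessability.

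**The case against.** **Safeguards.** The protocol has real ones: a statistician with no clinical involvement prepares the sequence, envelopes are numbered and opaque, they are opened only after baseline assessment, and monitors check recruitment procedures. These prevent swapping or reordering once an arm is seen. They do not prevent someone from deducing the next arm before a patient is enrolled.

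**Wording.** The phrase may be a slip for randomly permuted blocks of 4, or a garbled reference to varying sizes. That is possible, and it is why the sentence needs correcting either way. As it stands, it supports only a size of 4.

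**Knowledge of the block size.** A reader might infer that recruiters did know a third of the assignments because the size was published. The documents do not support this. The article's own citation is dated 2013, whereas the planned window is May to November 2011. Nothing shows that a document held at the sites stated the size, or that the researcher who opens envelopes also recruits. The size would have to be learned from a site document or inferred from the unblinded sequence, and a tally would have to be kept.

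**Size of bias.** A reader might also put a figure on it. If every certain assignment were exploited and expected response shifted by d points in opposite directions in the two arms, the bias would be (1/3)(2d): 0 for d = 0, 0.67 for d = 1 and 2.0 for d = 3. Against the 6.65-point target, the last two are 10% and 30%. No value of d comes from the documents, full exploitation at all four centres is an extreme case, and baseline adjustment would remove some of the effect. These numbers show how bias would scale and are not an estimate.

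**Conclusion.** The point stands as a conditional risk. As written, the protocol fixes blocks at 4 under conditions in which past assignments are visible at the centre. A person who knows or infers the size and follows one list can be certain of up to one third of upcoming assignments: 33.3% with complete blocks, and about 29% to 33% under the assumed centre lists and strata. Envelopes held at each centre suggest local lists, but the protocol does not say so, and blocks shared across centres would lower the figure.

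Nothing in the documents shows that anyone predicted or exploited an assignment. The size of any resulting bias cannot be derived from them and ranges from zero upward. The point deserves action because the weakness is cheap to remove beforehand, hard to repair afterwards, and at odds with the weight that the Discussion gives to concealment.

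**What to change.** 1. Generate the list with randomly varying permuted blocks, for example 4 and 6 in random order, within each Kellgren/Lawrence stratum at each centre.
2. Replace the sentence on block size with a statement that sizes vary and are not disclosed to the sites. State there that lists are separate by centre and grade, and how the grades are grouped.
3. Keep the sizes and their order in the statistician's restricted randomisation file, outside any protocol or manual that sites hold.

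If varying sizes were always intended, only the wording and the handling of the sizes need to change.

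**Gain:** assignments known with certainty fall from 33.3% to about 6%, or from about 71 to about 12 of 212 before allowing for incomplete blocks. Best-guess success falls only from 70.8% to about 69%, so this does not make the sequence unguessable.

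**Cost:** one rerun of the list in SAS before envelopes are packed. The largest possible imbalance at the end of a stratum rises from 2 to 3.

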and the points used in our previous pilot study. The moxibustion group will receive moxibustion treatment on the affected knee(s) at 6 standard acupuncture points (ST36, ST35, ST34, SP9, Ex-LE04, and SP10) plus up to 2 points of 'ashi', if needed, according to the determination of the practitioners (Figure 3). The moxibustion group will also receive the care provided to the usual care group.

Usual care

According to pragmatic design, the control group will not use a placebo procedure. Both the moxibustion and usual care groups will be allowed to use any type of treatment desired, including surgery, conventional medication, physical treatment, acupuncture, herbal medicine, over-the-counter drugs, and other active treatments. However, the participants will be asked to inform the research investigators of any new treatments performed after entry into the trial. Educational materials explaining KOA and self-exercise will be provided to each group. The participants in both groups will perform self-exercise, which consists of 1) stretching the hamstrings, biceps femoris, and ankles on both sides 3 times per day and 2) muscle exercises for the hamstrings and biceps femoris (including isometric and isotonic exercises) on both sides according to the disease status during the trial period.

Outcome

Primary outcome measurement

The primary outcome with respect to the effectiveness on KOA will be the mean change in the global scale value of the Western Ontario and McMaster Osteoarthritis Index (WOMAC) from baseline to 5 weeks. The WOMAC is

[figure not shown]

**Figure 2 Moxibustion device.** A photograph of the moxibustion device that will be used in this trial. This moxibustion device is a sticker-type disposable moxa, which functions for 5–10 minutes and is used for local acupuncture points. M: the upper part of the carbonised mugwort, A: adhesive sticker, H: height (2.1 cm), D: distance (1.9 cm).

[figure not shown]

**Figure 3 Acupuncture points of treatment.** The right knee will be treated at 6 standard acupuncture points (ST36, ST35, ST34, SP9, Ex-LE04, and SP10). The left knee will be treated with an additional point of 'ashi', which is located between ST35 and Ex-LE04. A: additional points of 'ashi' according to the determination of the practitioner. A Written consent for the picture was obtained from the pictured subject. Photograph by [name].

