one of the most widely used instruments and is composed of 24 questions to assess disability related to osteoarthritis. It includes 3 subscales to measure pain (5 questions), stiffness (2 questions), and physical function (17 questions) in KOA, and higher scores indicate more severe impairment [26,27]. There is a Korean version of the WOMAC (K-WOMAC), and Bae *et al.* confirmed its reliability, validity, and responsiveness [28]. We will therefore assess participants at the second visit (before starting moxibustion treatment) and at 5 weeks and 13 weeks from baseline using the K-WOMAC.

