**Table 1 Schedule for treatment and outcome measurements**

|                                    | Period | S |   |   |   |   |   |   | T |   |    |    |    |    |    | F  |
|------------------------------------|--------|---|---|---|---|---|---|---|---|---|----|----|----|----|----|----|
|                                    | Visit  | 1 | 2 | 3 | 4 | 5 | 6 | 7 | 8 | 9 | 10 | 11 | 12 | 13 | 14 | 15 |
|                                    | Week   | 1 | 1 | 1 | 1 | 2 | 2 | 2 | 3 | 3 | 3  | 4  | 4  | 4  | 5  | 13 |
| Informed Consent                   |        | • |   |   |   |   |   |   |   |   |    |    |    |    |    |    |
| Demographic Characteristics        |        | • |   |   |   |   |   |   |   |   |    |    |    |    |    |    |
| Medical History                    |        | • |   |   |   |   |   |   |   |   |    |    |    |    |    |    |
| Knee X-Ray                         |        | • |   |   |   |   |   |   |   |   |    |    |    |    |    |    |
| Inclusion/Exclusion Criteria       |        | • |   |   |   |   |   |   |   |   |    |    |    |    |    |    |
| Conformity Assessment              |        | • |   |   |   |   |   |   |   |   |    |    |    |    |    |    |
| Treatment Expectancy Questionnaire |        | • |   |   |   |   |   |   |   |   |    |    |    |    |    |    |
| Blood Test                         |        | • |   |   |   |   |   |   |   |   |    |    |    |    | •  |    |
| Vital Signs                        |        | • | • | ○ | ○ | ○ | ○ | ○ | ○ | ○ | ○  | ○  | ○  | ○  | •  | •  |
| Change in Medical History          |        |   | • | ○ | ○ | ○ | ○ | ○ | ○ | ○ | ○  | ○  | ○  | ○  | •  | •  |
| Random Allocation                  |        | • |   |   |   |   |   |   |   |   |    |    |    |    |    |    |
| Moxibustion Treatment              |        |   | ○ | ○ | ○ | ○ | ○ | ○ | ○ | ○ | ○  | ○  | ○  | ○  |    |    |
| K-WOMAC                            |        |   | • |   |   |   |   |   |   |   |    |    |    |    | •  | •  |
| Beck Depression Inventory          |        |   | • |   |   |   |   |   |   |   |    |    |    |    | •  | •  |
| The Short-Form 36v2 Health Survey  |        |   | • |   |   |   |   |   |   |   |    |    |    |    | •  | •  |
| Pain Numerical Rating Scale        |        | • | • |   |   |   |   |   |   |   |    |    |    |    | •  | •  |
| Physical Function Test             |        |   | • |   |   |   |   |   |   |   |    |    |    |    | •  | •  |

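### Table 1 marks random allocation at visit 1, one visit before the baseline K-WOMAC, while the text puts it at visit 2 after all baseline assessments

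*Protocol*

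**What the plan says.** The text is explicit about both the visit and the sequence. Under *Randomisation and allocation concealment*, the protocol states: "Random allocation will be performed at the second visit for participants who provide informed consent and meet the criteria for inclusion". The same section adds: "The corresponding envelopes will be opened only after the enrolled participants have completed all baseline assessments". Under *Primary outcome measurement*, the baseline K-WOMAC is also placed at the second visit, before moxibustion begins.

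Table 1 gives a different visit. Its row "Random Allocation" carries one mark, in the visit 1 column, alongside consent, knee X-ray and the eligibility check. The rows for K-WOMAC, BDI, SF-36 and the physical function test are empty at visit 1 and first marked at visit 2.

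Allocation is not hidden from participants. The protocol says that "the researcher will open the corresponding envelope in front of the participant" and that "participants and practitioners will be aware of the allocation arm according to the routine care setting". The primary outcome is "the mean change in the global scale value of the Western Ontario and McMaster Osteoarthritis Index (WOMAC) from baseline to 5 weeks", and under *Statistical analysis* the ANCOVA also adjusts for the baseline value.

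**The concern.** The two places give opposite orders for allocation and the primary-outcome baseline. Under the text, the baseline K-WOMAC is complete before anyone knows the arm. Under Table 1, the participant has seen the envelope opened one visit earlier.

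The order matters because the K-WOMAC is self-reported and participants are unblinded. Blinding the assessor gives limited protection to a questionnaire that rests on the participant's own answers. The baseline is the one K-WOMAC measurement that can be kept free of knowledge of the arm. If it is taken after allocation, it becomes a post-randomisation variable. It would then enter the primary analysis twice, as the start of the change score and as the adjustment covariate.

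Nothing practical would stop a site from working in the table's order. The X-ray that supplies the Kellgren/Lawrence stratum and the eligibility check are both marked at visit 1.

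**Working it through.** **Step 1: set the two places side by side.**

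| Item | Text | Table 1 |
|---|---|---|
| Random allocation | Second visit | Visit 1 only |
| Envelope opening relative to baseline | After all baseline assessments | One visit before the first K-WOMAC, BDI, SF-36 and function-test marks |
| Baseline K-WOMAC | Second visit, before moxibustion | Visit 2 |

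The text and the table agree on when the baseline K-WOMAC is taken. They disagree only on allocation, so the conflict is confined to that row.

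**Step 2: could the mark have moved when the PDF was read?** The neighbouring rows suggest not. Consent and X-ray fall at visit 1, K-WOMAC falls at visit 2, and moxibustion is marked at visits 2 to 13. That is 13 - 2 + 1 = 12 sessions, the number in the text. A shift in this row alone is unlikely, though not excluded.

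**Step 3: does any stated figure depend on this?** The sample-size inputs, from *Sample size*, are a difference of 6.65, SD 15.4, two-sided 5% and 80% power:

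n per group = 2 × [15.4 × (1.960 + 0.842) / 6.65]² = 84.19, against 84 stated.

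The plan's figure is reproduced, and the visit of allocation does not enter it.

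**Step 4: what would a shifted baseline do? (Hypothetical.)** Let b be the difference between arms in mean baseline K-WOMAC caused by knowing the arm, and let β be the slope of follow-up on baseline. The protocol gives neither. Assume b = 1 to 3 points and β = 0.3 to 0.7.

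- Size of bias in the raw change score: b.
- Size of bias in the ANCOVA effect: β × b. This is the same whether the response is the follow-up score or the change.

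| b (assumed) | Raw change-score bias, as share of 6.65 | ANCOVA bias, β = 0.3 to 0.7 |
|---|---|---|
| 1 | 1/6.65 = 15% | 0.3 to 0.7 points |
| 2 | 2/6.65 = 30% | 0.6 to 1.4 points |
| 3 | 3/6.65 = 45% | 0.9 to 2.1 points |

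The ANCOVA range is therefore 0.3 to 2.1 points, or 0.3/6.65 = 5% to 2.1/6.65 = 32% of the target.

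For an unadjusted change-score test with 84 per group, and taking 15.4 as the SD of the change, the standard error is 15.4 × √(2/84) = 2.38. The two-sided type I error would be about 7.1%, 13.4% and 24.3% for b = 1, 2 and 3. These rates do not apply to the planned ANCOVA, where the bias is smaller by the factor β.

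**The case against.** The strongest reply is that the text already settles the matter, and does so twice. One sentence fixes the visit. The other fixes the sequence whatever the visit number. A site that opened an envelope at visit 1 would breach an explicit rule, so harm requires someone to follow one table mark over two clear sentences. This stands, and it lowers the severity. It does not remove the contradiction: the table is the trial's schedule, and monitors who check conduct against the protocol would find two rules.

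A second reply is that Table 1 is not reliable in every cell. Patient Global Assessment is marked at visit 2, although the text describes it as improvement from baseline, rated at 5 and 13 weeks. A misprint in the allocation row is therefore quite plausible. That is fair, but a misprint also calls for correction.

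Some stronger readings are tempting, and the document does not support them:

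- A reader might infer that baselines were, or will be, collected unblinded. The protocol does not show this. Nor does it say that sites work from the table rather than the text; it describes workshops, standardised methods across centres and monitoring.
- A reader might treat bias as certain once the arm is known. Bias arises only if that knowledge shifts answers differently between arms.
- A reader might attach a large figure, for example 0.7 × 5 = 3.5 points, or 53% of 6.65. Both factors are assumptions with no source in the protocol.
- A reader might expect participants to leave between visits 1 and 2 and so be randomised without a baseline. This is possible under the table's order, but both visits fall in week 1 and no loss figure is given for that interval.

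**Conclusion.** The point holds as an internal contradiction of moderate severity. It is not a flawed design choice, since the intended order is stated in the text and is sound. The consequence is conditional: it arises only if a site follows Table 1, and then only if knowing the arm moves baseline answers differently in the two groups.

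Neither the size nor the direction of any bias can be derived from the protocol. The ANCOVA range in the working shows what could be at stake under assumed values and is not an estimate. The finding also rests on the Table 1 mark having been read in its printed column, which the neighbouring rows make likely.

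**What to change.** Move the random-allocation mark in Table 1 from visit 1 to visit 2. State, by a footnote or by row order, that allocation follows the visit 2 baseline assessments (K-WOMAC, BDI, SF-36, pain NRS and physical function test) and precedes the first moxibustion session. The table then agrees with *Randomisation and allocation concealment*, which needs no change.

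The cost is one table cell and a short note to the four centres. Sample size, endpoint and analysis model are unaffected. Recording the time of envelope opening against questionnaire completion would let the sponsor show that the order was kept, but this is optional and not needed to resolve the contradiction.
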